#### Secondary Outcomes

To address the limitations of binary variables and capture broader metabolic health improvements, we have established a clear hierarchy of secondary endpoints:

Key clinical markers: these include the absolute change in body weight (kg) and BMI, body fat percentage, and metabolic markers (fasting blood glucose and lipid profiles). Weight metrics are automatically recorded via the Huawei Pro 3 smart scale.Implementation feasibility: feasibility is measured by device pairing success rate and intervention adherence. While participants are instructed to perform weekly weigh-ins and daily dietary logging, “Good adherence” for analysis purposes is operationally defined as completing ≥50% of expected weekly weigh-ins (ie, at least 2 weigh-ins per month) and logging dietary intake on ≥50% of days during the intervention period. Acceptability is assessed via the System Usability Scale (SUS) and semistructured interviews with 30 purposely selected participants (Multimedia Appendix 3).Psychosocial and functional outcomes: we use validated Chinese versions of psychometric scales with established reliability (Cronbach α>0.80) [33-42]:

Clinical symptoms: Patient Health Questionnaire-9 (PHQ-9) for depression, Generalized Anxiety Disorder-7 (GAD-7) for anxiety, Brief Psychiatric Rating Scale Version 4.0 (BPRS-4) for acute psychopathology, and Mood Disorder Questionnaire (MDQ) for mood swings.Functioning and quality of life: Sheehan Disability Scale (SDS) for functional impairment and Quality of Life Enjoyment and Satisfaction Questionnaire-Short Form (Q-LES-Q-SF) for life satisfaction.Cognitive and physical well-being: Perceived Deficits Questionnaire–Depression, 5-item (PDQ-D5) for subjective cognitive deficits, Chalder Fatigue Scale (CSF-11), Perceived Stress Scale (PSS), and Arizona Sexual Experience Scale (ASEX).Weight motivation: a 0‐100 mm Visual Analogue Scale (VAS) quantifies the intent to lose weight.

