## Methods

### Study Design

This study uses a pragmatic, open-cohort SW-CRT with a 2-month step duration. The trial spans a total observation window of 6 months across 6 clinical units at a tertiary hospital in Beijing. The SW-CRT design ensures that all participants eventually receive the intervention, fulfilling ethical requirements for this high-risk population, while the staggered rollout allows the implementation team to maintain high fidelity by providing intensive technical training for 1 wave at a time.

The trial addresses the dynamic turnover of psychiatric hospitalizations (average stay 4‐6 wk) by defining each cluster as a clinical unit rather than a fixed physical location. The research team comprises trained research assistants, certified nutritionists, and sports physicians. Participants are typically enrolled during their stable recovery phase in the ward; however, the intervention is designed to be portable. Following discharge, the intervention continues remotely, with the same clinical team providing longitudinal oversight via digital clinician dashboards. This approach enables the evaluation of the intervention across the transition from inpatient care to community-based recovery.

The 6 units were randomized into 2 waves (3 units per wave) using a matched-pair constrained randomization approach. To ensure baseline balance, units were paired based on clinical setting and demographics. Allocation was managed by an independent biostatistician via REDCap (Research Electronic Data Capture; Vanderbilt University) and remained concealed from the recruitment staff and participants.

The study timeline is structured into three distinct phases:

Baseline phase (month 1): all clusters receive usual care to establish stable baseline metrics.Transition phase (2 weeks): a staggered 2-week period for device distribution and technical training, occurring at month 1 for wave 1 and month 3 for wave 2.Intervention phase: active digital monitoring lasting 5 months for wave 1 (months 2-6) and 3 months for wave 2 (months 4-6).

This open-cohort approach accounts for the dynamic turnover of psychiatric hospitalizations, allowing for individual enrollment while maintaining randomization at the cluster level (Figure 2).

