### Patient Recruitment

Due to the dynamic turnover of psychiatric hospitalizations, an open-cohort approach was adopted, allowing for continuous recruitment throughout the study period. Recruitment follows a structured clinician-referral model across the 6 clinical units to ensure both clinical appropriateness and implementation fidelity. The process is organized into the following stages: Treating psychiatrists identify potential participants during routine clinical encounters in the outpatient and inpatient departments. Patients are considered for referral if they meet three prerequisites: (1) a BMI ≥24 kg/m², (2) a demonstrated interest in weight management, and (3) a confirmed stable clinical phase, defined as a minimum of 4 weeks on a stable medication regimen.

Upon referral, an independent project physician conducts a formal in-person screening session. This involves a review of the patient’s electronic health records (EHR) to confirm *ICD-10* (*International Statistical Classification of Diseases, Tenth Revision*) diagnoses and physical measurements of height, weight, and blood pressure. To ensure the validity of historical data, the exclusion criterion regarding significant prior weight loss is ascertained through a multi-informant approach, cross-referencing patient interviews with collateral reporting from family caregivers and EHR data. Detailed inclusion and exclusion criteria are summarized in Textbox 1.

Textbox 1.Inclusion and exclusion criteria.

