### Intervention Program

The SWIM intervention is a multicomponent digital health program grounded in SCT, designed to enhance self-regulation for weight management. Participants are provided with a Huawei Pro 3 Bluetooth-enabled smart scale and the Huawei Health App (v10.0.2) installed on their personal smartphones. The intervention is coordinated by a multidisciplinary research team, including a trained research assistant for technical setup, a certified nutritionist for dietary content, and a psychiatrist for clinical oversight.

The program follows a hybrid delivery model, initiating in the psychiatric inpatient units of Beijing Anding Hospital and continuing remotely in the participants’ community settings post discharge. During the 2-week transition period, participants receive in-person training on biometric tracking and dietary logging. The intervention lasts for the duration of the assigned wave (5 months for wave 1 and 3 months for wave 2). Participants are instructed to perform weekly weigh-ins and daily dietary logging. To support behavioral change, biweekly educational modules are delivered via WeChat (Tencent) groups. See Multimedia Appendix 1 for the smart scale setup guide and weighing protocol. Furthermore, weekly automated push notifications and personalized feedback messages are sent via messages, with content tailored to each participant’s specific weight trajectory (Table 1).

**Table 1. T1:** Summary of SWIM intervention components.

Components	Delivery method	Frequency
Smart scale weigh-ins	Digital Health App and compatible smart scale	Weekly (at least once per week)
Dietary logging	Digital Health App	Daily (all meals and snacks)
Education session	WeChat groups	Biweekly
Behavior enhancing	Message prompts and tips	Weekly (Automated push notifications and personalized feedback)

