### Outcomes and Measures

#### Overview

This study uses a Type 1 hybrid implementation-effectiveness framework to concurrently evaluate clinical outcomes and implementation feasibility. Assessments are conducted at Baseline (month 0) and follow-up intervals at months 1, 2, 3, and 6 (Multimedia Appendix 2). Data collection integrates EHR, laboratory tests, and structured assessments. Baseline assessments take approximately 60 minutes, with 25-minute follow-ups. To ensure long-term sustainability, we use a tiered engagement protocol for nonadherence: automated reminders, followed by counselor outreach (after 2 wk), and finally in-person support for persistent cases. Technical support is provided via video tutorials and a dedicated hotline.

Financial incentives are avoided to favor clinically translatable behavior reinforcement strategies. To address the risk of multiplicity and ensure statistical rigor, we have established a clear hierarchy of endpoints.

To address the risk of multiplicity and ensure statistical rigor, we have established a clear hierarchy of endpoints.

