### Ethical Considerations and Data Security

This study was conducted in strict accordance with the Declaration of Helsinki and received formal ethical approval from the Ethics Committee of Beijing Anding Hospital (Approval No. [2022] Research [202]-202321FS-2). Given the vulnerability of the SMI population, a structured, multistage informed consent process was implemented. Potential participants underwent a capacity assessment by their treating psychiatrist to ensure they understood the study’s nature and risks. We used the Teach-back method, where participants were asked to explain the study’s core components in their own words to verify comprehension. For participants with partial capacity, written informed consent was obtained from both the participant and their legally authorized representative (primary caregiver).

To mitigate risks associated with the use of a proprietary app (Huawei Health), we have implemented a data-decoupling protocol. Researchers do not have access to participants’ cloud accounts or backend data. Instead, de-identified metrics (weight and BMI only) are submitted via encrypted WeChat Enterprise Edition (TLS 1.3) channels. Redacted data are stored on password-protected hospital servers using Advanced Encryption Standard (AES)-256 encryption with 2-factor authentication. Access logs are maintained for auditing, and all study-specific digital data will be permanently deleted 6 months post-completion, adhering to the minimum necessary period principle.

To address the risk of technological failure (eg, server downtime or software bugs), a manual backup procedure is in place. Participants are instructed to read weight values directly from the smart scale’s LED display and record them in a provided paper log or via encrypted messaging. Paper-based food diaries will serve as a contingency tool for dietary logging. This dual-track system ensures continuity of data collection and minimizes reliance on a single digital interface.

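### The recorded weight source appears to change at crossover, so a scale offset in either direction would be confounded with the treatment effect in the phase comparison

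*Protocol article*

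**What the plan says.** Under Secondary Outcomes the protocol article states: "Weight metrics are automatically recorded via the Huawei Pro 3 smart scale". The section on the Intervention Program makes that scale part of the intervention ("Participants are provided with a Huawei Pro 3 Bluetooth-enabled smart scale"). Study Design places its handout in "a staggered 2-week period for device distribution and technical training, occurring at month 1 for wave 1 and month 3 for wave 2". Before that, "all clusters receive usual care to establish stable baseline metrics".

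The only weighing described before crossover is at screening, where the project physician takes "physical measurements of height, weight, and blood pressure". No instrument is named.

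The Outcomes overview schedules assessments at months 0, 1, 2, 3 and 6 and adds: "Data collection integrates EHR, laboratory tests, and structured assessments". It does not say which of these supplies weight. Table 2 mentions laboratory tests and surveys at visits, but no weighing. If the technology fails, participants read the smart scale's display and "record them in a provided paper log or via encrypted messaging", so the backup uses the same device.

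The primary outcome is loss of at least 5% from baseline at month 6, and that section names no weight source. The Primary Objective and the Clinical Effectiveness Analysis compare intervention with control phases.

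Body fat percentage is among the key clinical markers. The data-security section says that researchers have no access to backend data and that the submitted metrics are limited to weight and BMI.

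**The concern.** A stepped-wedge analysis estimates the treatment effect from the change that occurs when a unit crosses over. If the instrument that records the outcome changes at the same moment, the two changes are one change as far as the model can tell. Weight is the quantity behind the primary outcome and the kg and BMI outcomes, and a 5% threshold is sensitive to small shifts. A difference of about a kilogram between a ward scale and a personal smart scale would matter against the effects this trial is sized to detect.

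This goes beyond missing detail. The article names one recorder of weight, and that recorder cannot serve participants who have not yet been given it.

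**Working it through.** There is no stated figure to reproduce. Two checks apply.

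**1. Can the model separate device from treatment?**

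Let X = 1 in intervention periods and D = 1 when weight is read on the smart scale. If control weights come from another source:

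| | Wave 1 | Wave 2 |
|---|---|---|
| Control (X = 0, D = 0) | before its month-1 transition | before its month-3 transition |
| Intervention (X = 1, D = 1) | months 2-6 | months 4-6 |

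D equals X in every unit and period; their correlation was 1.0 in each of four period layouts tried. With a true effect β1 and a device offset θ, the model contains β1·X + θ·D = (β1 + θ)·X, so only the sum is estimable. Categorical time, time since crossover, medication-risk group and the random intercepts do not break this identity. Time since crossover describes a trend after the switch, not the step at the switch.

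The scheduled assessments at which the waves are in different conditions are months 2 and 3 (month 3 is when wave 2's transition falls). Those are the visits at which the weight sources would differ. At month 6 both waves have the scale, so a common offset largely cancels between waves there.

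**2. How large could it be?**

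From the protocol: 20% success in control, 40% in intervention, target d = 0.40. Assumed, because the protocol gives none: body weight 80 kg, percentage change normal with mean -0.8 and SD 5, and the size of the offset.

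P(change ≤ -5) = Φ((-5 - mean)/5).

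- No offset: Φ(-4.2/5) = Φ(-0.84) = 20.0%.
- 1 kg is 100 × 1/80 = 1.25 points.
- Scale 1 kg low: mean -2.05, Φ(-2.95/5) = Φ(-0.59) = 27.8%.
- Scale 1 kg high: mean +0.45, Φ(-5.45/5) = Φ(-1.09) = 13.8%.

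| Offset | Responders, scale low | Responders, scale high |
|---|---|---|
| 0.5 kg | 23.7% | 16.7% |
| 1.0 kg | 27.8% | 13.8% |
| 1.5 kg | 32.1% | 11.2% |

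With the control rate held at 20% and the assumptions varied over 75-95 kg and SD 4-8 points, a 1 kg offset gives 23.9-30.6% (low) or 12.0-16.5% (high).

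For the kg outcome, a constant 1 kg offset moves the estimate by 1 kg. If the SD is 3-6 kg (assumed), d = 0.40 is 0.40 × 3 = 1.2 kg to 0.40 × 6 = 2.4 kg, so 1 kg is 1/2.4 = 42% to 1/1.2 = 83% of the target effect.

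**3. Body fat.** Secondary Outcomes makes it an outcome, while the data-security text allows only weight and BMI through to the researchers. Read together, smart-scale body fat would reach the analysis in neither phase, and no other source is named.

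**The case against.** The strongest reply is that the control-phase weight source is not stated, so a switch is an inference. The article lists the electronic record among its data sources and refers to a visit schedule in Multimedia Appendix 2, which is not shown. A staff weighing common to both phases is compatible with the text. This stands, and it makes the conclusion conditional. It does not remove the point, because the sentence that names a recorder names one that control participants do not have.

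The smart-scale sentence also sits under the secondary outcomes, and the Primary Outcome section names no source. Applying it to the primary outcome is reasonable but inferred. At a pure month-6 comparison between waves, a common offset would largely cancel. The exposure lies in the control-versus-intervention comparison that the objective and the model describe.

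The planned multiple imputation, pattern mixture models and tipping point analysis deal with missing weights. They do not address a change of instrument.

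A reader might infer more than the documents support:

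- That a device offset would show up as weight loss. This is so only if the smart scale reads lower than the other source; if it reads higher, it hides loss. Neither sign nor size is documented.
- That clothing, time of day and setting also change at crossover. Nothing says so. The intervention starts on the wards, and a weighing protocol is cited in Multimedia Appendix 1 (not shown).
- That weights are routinely hand-recorded. The paper log is a backup for technical failure.
- That weights are informatively missing in one phase only. This is not established.
- That body fat simply lacks control data. The firmer point is the conflict between the two sections.

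**Conclusion.** The point holds in conditional form. As the article is written, the named weight recorder arrives with the intervention. Unless a common visit weighing exists elsewhere, a device offset is fully confounded with the treatment effect in the phase comparison, and no planned covariate or missing-data analysis can separate them.

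The direction is unknown. Under the stated assumptions a 1 kg offset shifts the responder proportion by about +8 or -6 points against a planned 20. The offset, body weight and SD are illustrative; the protocol gives none of them. It is not shown that the primary result is biased, only that the document leaves it open to such bias.

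The body fat conflict stands on the text alone.

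**What to change.** Define the primary (at least 5%), kg and BMI outcomes from one weight source in both phases: staff-measured or electronic-record weights at months 0, 1, 2, 3 and 6. Keep smart-scale weights for adherence and for a sensitivity analysis, with an offset estimated from paired readings where both exist. Correct the Secondary Outcomes sentence to match, and reconcile its automatic recording with the submission route in the data-security section.

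If no common source exists, report the phase comparison with an offset sensitivity analysis in both directions, and state that limitation.

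For body fat percentage, name a source available in both phases or remove it as a comparative outcome.

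Cost: where common weights exist, this is a change of endpoint wording and data extraction. Some visits may lack a staff or electronic-record weight and will rely on the planned imputation. The Results section reports that follow-up has finished, so weighings that were never made cannot be added. Study-specific digital data are to be deleted 6 months after completion, so any paired readings should be extracted before then.

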### Ethical Considerations and Data Security

This study was conducted in strict accordance with the Declaration of Helsinki and received formal ethical approval from the Ethics Committee of Beijing Anding Hospital (Approval No. [2022] Research [202]-202321FS-2). Given the vulnerability of the SMI population, a structured, multistage informed consent process was implemented. Potential participants underwent a capacity assessment by their treating psychiatrist to ensure they understood the study’s nature and risks. We used the Teach-back method, where participants were asked to explain the study’s core components in their own words to verify comprehension. For participants with partial capacity, written informed consent was obtained from both the participant and their legally authorized representative (primary caregiver).

To mitigate risks associated with the use of a proprietary app (Huawei Health), we have implemented a data-decoupling protocol. Researchers do not have access to participants’ cloud accounts or backend data. Instead, de-identified metrics (weight and BMI only) are submitted via encrypted WeChat Enterprise Edition (TLS 1.3) channels. Redacted data are stored on password-protected hospital servers using Advanced Encryption Standard (AES)-256 encryption with 2-factor authentication. Access logs are maintained for auditing, and all study-specific digital data will be permanently deleted 6 months post-completion, adhering to the minimum necessary period principle.

To address the risk of technological failure (eg, server downtime or software bugs), a manual backup procedure is in place. Participants are instructed to read weight values directly from the smart scale’s LED display and record them in a provided paper log or via encrypted messaging. Paper-based food diaries will serve as a contingency tool for dietary logging. This dual-track system ensures continuity of data collection and minimizes reliance on a single digital interface.

### Adverse Events

Trial safety is overseen by an independent steering committee. Serious adverse events, including life-threatening incidents, psychiatric hospitalizations, or serious violent incidents, are reported within 24 hours. Recognizing the potential for digital-specific harms in the SMI population, we have transitioned from a reactive to a preventive monitoring framework. A dedicated data safety officer reviews unblinded adherence data monthly. “Red flag” patterns, such as obsessive weighing (>3 times/day) or a sudden cessation of logging after high engagement, will trigger an immediate clinical welfare check. We explicitly monitor for increased anxiety surrounding weigh-ins, worsening body image concerns, and digital fatigue. The emotional experience of app usage will also be explored during semi-structured exit interviews with a subset of participants. Should psychosocial distress be identified, a predefined supportive protocol is activated, including counseling to reframe the intervention as a supportive tool and practical adjustments to monitoring frequency. The digital intervention will be discontinued for any participant demonstrating (1) a clinically significant increase in psychiatric symptoms (eg,> 20% increase in BPRS-4 scores), (2) the emergence of technology-related delusions, or (3) new-onset disordered eating behaviors. All adverse events will be assessed for their relationship to the trial in accordance with HRA requirements and reported in the final study results.

### Intervention Checkpoints

The intervention checkpoints are presented in Table 2.

**Table 2. T2:** Intervention checkpoints.

Components	Checkpoints
Participants	Setup: successfully install the study app and pair the Bluetooth-enabled smart scale. Core usage: demonstrate competency in weight logging and food diary recording. Perform weekly self-weighing and dietary tracking as instructed. Follow-up compliance: complete lab tests and surveys at designated visits upon receiving notifications.
Study app	Data visualization: upon data entry (weight and diet), the app generates weight trajectory charts and dietary gap rainbow. Data security: automatically encrypt and transfer response data to HIPAA^a^-compliant servers.
Research team	Routine motivation: send scheduled external reminders (via phone messages) to prompt weekly weighing and dietary recording. Retention: monitor the clinician dashboard for inactivity. Initiate counselor calls or clinic visit invitations if participants miss >2 scheduled weigh-ins. Visit: manually track and notify participants monthly to complete required questionnaires and lab tests.

a HIPAA: Health Insurance Portability and Accountability Act.

